## Abstract

The aim of this study is to investigate circadian rhythms in independently living adults with obesity and mental disease, exploring the interplay between biological markers and lifestyle factors. Eighty participants divided equally into four groups; (i) people with obesity and schizophrenia; (ii) people with obesity and bipolar disorder; (iii) people with obesity without mental disease or sleep disorders, and (iv) people without obesity, mental disease or sleep disorders. Over two consecutive days, participants engage in repeated self-sampling of hair follicle and saliva; concurrently, data is collected on diet, body temperature, light exposure, sleep parameters, and physical activity by accelerometry. Hair follicles are analyzed for circadian gene expression, saliva samples for cortisol and melatonin concentrations. Circadian rhythms are investigated by cosinor analysis. The study employs a participant-tailored sampling schedule to minimize disruptions to daily routine and enhance ecological validity. The methodology aims to provide a comprehensive insight into the factors contributing to circadian disruptions in people with obesity, bipolar disorder and schizophrenia, potentially informing strategies for future management and mitigation.

**Trial registration:** (ClinicalTrials.gov Identifier: NCT05413486).

## Introduction

This study protocol provides a comprehensive overview of the study procedures and methods in the Sleep, Obesity and Mental Disease—Biological Markers for the Evaluation of Circadian Rhythmicity (SOMBER) trial (ClinicalTrials.gov Identifier: NCT05413486). The study procedure for the SOMBER trial is outlined in Fig 1.

**Fig 1 pone.0306408.g001:**
[figure not shown]
Schedule of enrolment and assessments at all time points in the SOMBER Trial.

### Background

Circadian disturbances have emerged as a significant health concern with profound implications for human well-being. From endocrine [1], cardiovascular [2] and immune function [3] to energy homeostasis, digestion, metabolism [4] and cell signalling [5], practically all aspects of human physiology are affected by the relative time-of-day in relation to the natural human sleep-wake cycle. Modern-day societal norms and advancements in technology have led to widespread disruptions of the circadian rhythm: Night time light pollution [6], shift work, irregular sleep schedules and jet lag all contribute to these disruptions [7]. Circadian misalignments are known to contribute to a variety of psychiatric disorders, creating a bidirectional relationship, where mental health issues can predispose individuals to poor sleep quality, which in turn may exacerbate symptoms of the underlying disorder, such as heightened anxiety and increased rumination. This cycle can further complicate sleep patterns, making it more challenging to achieve restful sleep [7,8]. Disruptions to the circadian cycle not only aggravate the symptoms of mental diseases but likely also play a significant role in triggering first symptoms at onset [9].

The suprachiasmatic nuclei (SCN) are the brain’s central circadian pacemakers primarily entrained through non-visual photosensitive retinal ganglion cells when sun light hits the retina. Human circadian rhythms are thus aligned with the light-dark cycle. Even in the absence of light stimulus, this rhythm is maintained in part by so-called clock genes, which generate self-sustaining circadian oscillation through positive and negative transcriptional/translational feedback loops. Clock genes work both in concert with and independently of the SCN [10] and multiple diseases are linked to abnormal clock gene function.

In schizophrenia (SCH), clock gene disruption has been demonstrated for *CRY1* and *PER2* in skin fibroblasts, *PER1/2/3* and *NPAS2* in white blood cells, and in post-mortem analyses for P*ER1/2*, *CRY2*, and *NR1D1* in the prefrontal cortex [11–13]. Similarly, in bipolar disorder (BD), whole blood analysis have revealed reduced expression of *CRY 1/2*, *PER 1/2/3* and *ARNTL* during depressive episodes [14]. Similar results have been reported for clock genes in skin fibroblast [15].

A common denominator of both mental disease and circadian disturbances is the link with obesity [16,17]. Circadian disturbances, mental disease and obesity seems to form a tridirectional relationship where symptoms or condition-related disease severity may alter the progression of either one or both of the other two conditions. For example, in schizophrenia, anti-psychotic medicine often lead to weight gain and increased obesity risk [18]. Obesity in turn increases the risk of sleep disturbances (e.g., poor sleep quality and/or obstructive sleep apnoea (OSA)) [19]. Sleep disturbances may then both make the patient more susceptible to emotional instability [20] as well as obesity e.g., by triggering emotional eating or leading to increased night-time snacking [16]. Meal timing, diet, social cues, media device usage, and light exposure are just some of the factors influencing, and influenced by, circadian disruptions, which may in turn lead to obesity [21]. Both obesity and schizophrenia are associated with increased levels of tumor necrosis factor-α and other pro-inflammatory cytokines with established impact on the physiological regulation of sleep [19,22]. These cytokines ordinarily follow a circadian rhythm, which may be disturbed in people with obesity and sleep disorders [19]. In addition, several clock genes commonly disrupted in schizophrenia have been shown to play a key role in energy and lipid metabolism [23–25]. Altogether, the tridirectional relationship between circadian disturbances, mental disease and obesity is complex and consist of several interloping vicious cycles. Fig 2 presents some examples of intermediate pathways between circadian disturbances, mental disease and obesity.

**Fig 2 pone.0306408.g002:**
[figure not shown]
The tridirectional relationship between circadian disturbances, mental disease and obesity. Circadian disturbances, mental disease and obesity are associated through a complex network of intermediating factors, each potentially influencing or being influenced by other factors in the network.

Circadian rhythms in humans can be evaluated through various biomarkers, including hormonal peak values and rhythms, daily body temperature changes, and rhythmic gene expression [26]. Since circadian rhythms are closely intertwined with daily routines, measurements taken in laboratories or in-hospital settings may have low ecological validity due to the impact of these artificial environments. Therefore, there is a need for minimally invasive sampling techniques, compatible with daily routines, which can be applied in a real-life setting.

The primary aims of this study are to: (i) To investigate biological markers of disturbed circadian rhythm in free-living adults with obesity and schizophrenia or BD using non-invasive methods and; (ii) to compare biological markers of disturbed circadian rhythm with subjective and objective measures of sleep quality.

### Recruitment

Participants are primarily recruited at the obesity clinic at the University Hospital, Southern Denmark, Esbjerg and through local out-patient psychiatric treatment units and patient networks. Psychiatric out-patients are referred to the study by health professionals aware of the trial design. Additional non-obese controls are recruited through online postings on social media. Recruitment started April 2022 and is scheduled to complete by August 2024. All study procedures are in adherence with the principles of the Declaration of Helsinki and approved by the Regional Health Ethics Committee (S-20210181 with amendments). Written Informed consent was obtained from all participants. The investigator is responsible for obtaining informed consent and enrolling patients in the study.

### Study procedure

Participants will visit the clinic three times. Between clinical visit 1 and 2, participants will collect saliva and hair follicles over a 2-day period. In addition, participants will wear accelerometers and continuous glucose monitors (CGMs) for a total of 8 days. The study procedure is outlined in Fig 1 and detailed chronologically below.

#### Clinical visit 1

During the first clinical visit, data will be gathered on anthropometry (height, weight, body composition (by bioimpedance (InBody770®, InBody, Seoul, Korea)), hip and waist circumference), physical function (grip strength (by hand dynamometer (Kern & Sohn, Balingen, Germany)), 10 m usual and maximal gait speed, 1-leg standing balance) and patient-reported outcomes (intake of caffeinated drinks, alcohol consumption, habitual use of sleep medications, socioeconomic status, living arrangements, education, ethnicity, hair-colour, co-morbidities and sleep quality (PSQI [27]).

After initial testing, accelerometers (Axivity AX3, Axivity Ltd., Newcastle upon Tyne, United Kingdom) and CGMs (Freestyle libre-2, Abbott Laboratories, Lake Bluff, Illinois, USA) are mounted and the participant is given thorough instruction on how to record dietary intake and self-sample (See “data collection” below). Self-sampling will be performed at the time points outlined in Fig 3. Participants are provided with all necessary equipment (sampling tubes, manuals, camera, tweezers and scissors). The two sampling days will be placed within 1–5 days of the first clinical visit. Importantly, participants are asked to choose two days with an ordinary daily rhythm, especially in regards to sleep and wake time and to avoid irregular days (e.g., celebratory events or holidays). Manuals, protocols and trial-specific questionnaires utilized during clinical visit 1 are available as (S1–S3 Files).

**Fig 3 pone.0306408.g003:**
[figure not shown]
Example of sampling schedule. Above schedule assumes a wakefulness period of seventeen hours. Schedules are adjusted relative to individual rhythms. Participants are instructed to start sampling of hair follicles and saliva at awakening and every six hours hereafter, as well as one sample at bed time. Additional saliva samples are collected every two hours after twelve hours wakefulness and approximately one hour before bedtime. Oral temperature is measured concurrently with saliva sampling.

#### At-home testing

For two consecutive days participants will sample saliva approximately six times (depended on wakefulness period) per day, hair samples four times per day and record body temperature and dietary food intake (S1 File). Participants are provided with an individualized schedule indicating all sampling times. Participants will collect saliva by a chewable saliva collector (Salivette Cortisol saliva collector, Sarstedt, Nümbrect, Germany). Saliva sampling entails placing one (or two in case of xerostomia, common with some psychotropic drug [28]) small moisture absorbing cottonous tube in the mouth which is then spat into a test tube and refrigerated. Participants are instructed to avoid food or drinks 30 minutes before saliva sampling, and to follow their normal meal times. Oral temperature are collected simultaneously with saliva sampling using an oral thermometer according to manufacturers’ instructions (Apotekets, Skovlunde, Denmark). Hair follicles are self-sampled with tweezers. Participants will pluck 20 hairs from the scalp or chin and place these in a date- and time marked tube containing dissolution buffer (RNeasy Micro Kit; QIAGEN, Hilden, Germany). Immediately after sampling, follicle- and saliva samples are placed in the refrigerator. If participants need to collect samples away from their home they are provided with cooling bags and icepacks.

During each of the two home-sampling days, participants are offered home visits from a study representative, a health professional trained in collecting hair follicles. If the participant declines this offer, telephone meetings are scheduled instead. If possible, home visits will be scheduled around a sampling time, during these visits the sample is collected by the study representative. This is to allow for comparison between self- and professional- sampling. During visits, additional data is gathered on light exposure and media device screen time usage (S4 File), and any potential safety concerns are noted and dealt with as applicable under the regulations for out-patient treatment.

#### Clinical visit 2

Following the two sampling days, participants will again meet at the clinic. Participants are asked to fill in the Morningness-Eveningness Questionnaire (MEQ) and a brief questionnaire on their experience on how easy/troublesome they found different aspects of sampling.

#### Clinical visit 3

At the final visit, a time for at-home sleep apnoea screening is scheduled. Sleep apnoea is tested for using a Nox-T3 sleep apnoea screening kit (Nox Medical, Reykjavik, Iceland). As this last visit only requires the participant to receive a 5-minute introduction in using the NOX-T3 equipment and dropping off accelerometers, this visit may instead be handled as a home visit. To avoid unnecessary tests, participants with recent (<6 months) apnoea screening available from registries are not re-assessed, unless there is reason to suspect a change in apnoea status, e.g., excessive weight loss/gain or change in medication.

#### Information from patient registries

Supplementary information is collected from patient registries. This includes use of prescription medicine, active diagnoses, health and disease screenings, blood samples and questionnaire responses, of note the Epworth Sleepiness Scale [29] and the Berlin Questionnaire, both sleep related questionnaires used to screen for sleep apnoea [30].

A summary schedule of study outcomes is presented in Table 2.

**Table 2 pone.0306408.t002:** Summary of all data gathered at all time points and from registries.

	Clinical visit 1	Home visit 1	Home visit 2	Clinical visit 2+3	From patient registries
*Data gathered*	• Anthropometrics • Physical function	• Clock gene expression• Cortisol rhythm• Melatonin rhythm• Food Diary• Oral temperature• Oral Ph	• Clock gene expression• Cortisol rhythm• Melatonin rhythm• Food Diary• Oral temperature• Oral Ph	• Sleep apnoea screening	• use of prescription medicine • Lipid and hormonal blood profiles • body composition
	Questionnaire data: • Sleep Quality • Oral sleep aids • Daily coffee and alcohol intake • Job situation • Living arrangement	Questionnaire data: • light exposure • screen time • sample-day 1 wake and sleep time	Questionnaire data: • light exposure • screen time • sample-day 2 wake and sleep time	Questionnaire data: • Participant feedback • Chronotype	Questionnaire data: • Tiredness and sleep • Lifestyle • Habits • Pain
	Continuous objective measures (8 days, starting clinical visit 1): • Sleep amount and quality by accelerometer • Skin surface temperature changes by accelerometer • Daily glucose patterns (by continuous glucose monitor)				

#### Patient monitoring and safeguards

Throughout the sampling period, we maintain regular contact with participants to promptly address any signs of undue stress, discomfort, or negative health findings. Our protocol includes daily follow-up communications on sampling days. Should any adverse events or critical health findings arise, early termination may be considered, and participants may be directed to appropriate health treatment facilities for further evaluation or treatment.

### Laboratory analyses

All laboratory tests are performed by researchers blinded to all other outcomes and group allocations.

#### Saliva hormonal analyses

Within 24–72 hours after sampling, samples are centrifuged at 2000g for 5 minutes. Immediately afterward, they are stored at -80°C until analyzed for cortisol, melatonin, and pH at the Department of Clinical Biochemistry, Copenhagen University Hospital, Rigshospitalet, Glostrup, Denmark. For cortisol analysis, 200 μl of saliva is analyzed using an IDS-iSYS Multi-Discipline Automated System (Immunodiagnostic Systems, Tyne & Wear, United Kingdom) with the CE-labeled Salivary Cortisol kit (IS-4900). Where possible, the pH of the saliva samples analyzed for cortisol is measured using a standard pH electrode (Mettler-Toledo FiveEasy, Leicester, United Kingdom); samples for pH measurement undergo one additional freeze-thaw cycle before analysis. Melatonin is quantified using 2x50 μl of saliva with the CE-labeled Saliva ELISA kit (IBL International, Hamburg, Germany), in combination with a standard ELISA reader (Perkin Elmer 1420 Victor 3 Multi Label Counter; Shelton, Connecticut, USA). If the saliva volume is insufficient for both cortisol and melatonin analyses, cortisol is prioritized.

#### Hair follicle clock gene expression

All hair follicles are analyzed at Steno Diabetes Center Odense, Odense, Denmark. After collection during home visits the samples are stored at -80° C until further analysis. RNA from the hair follicles is isolated using an RNeasy Micro kit (QIAGEN, Hilden, Germany) according to the manufacturer’s instructions. Briefly, the samples are thawed on ice after which they are centrifuged to precipitate the hair follicle cells. After removing the supernatant, the cells are lysed using a RLT buffer supplemented with DTT. The lysates are then processed through spin-columns, treated with DNase (Qiagen, Denmark) to remove genomic DNA, washed with RW1 and RPE buffers, and subjected to ethanol precipitation. The final RNA is then eluted in a minimal volume of RNase-free water and quantified by NanoDrop spectrophotometer (Thermo Fisher Scientific, Waltham, MA). RNA is reverse transcribed to cDNA using a high-capacity cDNA reverse transcription kit (Applied Biosystems, Foster City, CA) according to manufacturer’s protocol. The qPCR is performed on a QuantStudio 5 real-time PCR system (Applied Biosystems, Foster City, CA) using the pre-designed commercially available TaqMan Custom Arrays (Applied Biosystems, Foster City, CA). All samples are run in triplicates. We will test the gene expression of a panel of circadian rhytm-related genes (e.g. *PER3*, *NR1D1/2*). The expression of any genes of interest will be normalized to appropriate reference genes. We will test a panel of reference genes to identify the most appropriate and stable candidates.

### Data handling and analyses

Data will be hosted and handled in accordance with Danish law and regulation. The trial dataset is accessed by the investigators ([name] and [name]). [name] will perform the data analyses and takes responsibility for the data integrity. All data files are retained for 5 years after the study’s conclusion, after which they will be either anonymized or deleted.

#### Main outcomes

The primary outcome is circadian expression of clock-genes, the secondary outcomes are circadian salivary cortisol and melatonin rhythms.

#### Power calculation

Based on Sun et al. (2016) [12], and targeting a statistical power of 0.8 and an alpha error of 0.05, our study requires groups of 17 participants for the mesor and 16 participants for the amplitude to show statistically significant group differences in clock gene expression, as measured by unpaired t-tests.

#### Statistical analyses

The four observational groups will be compared on group characteristics of e.g., BMI, body composition, physical function and SES using One-Way Analysis of Variance (ANOVA) or Kruskal-Wallis tests for continuous or ordinal outcomes, and Chi-squared statistics for categorical outcomes as dictated by model assumptions and applying suitable post-hoc analyses as appropriate.

The primary outcome will be analyzed for each study group. Rhythmicity will be assessed by approximating each individual’s 48-hour profiles to a 24 hour cosine wave function in non-linear mixed effects models thereby allowing for the estimation of amplitude, acrophase, and mesor for each group. Derived variables will be compared between groups using the non-obese control group as the reference. Inter-day variability of circadian parameters will be analyzed for each group. Cosine analyses will be individualized relative to participants objectively measured mean sleep offset time.

The same procedure will be used for the secondary measures of rhythmicity i.e. salivary cortisol and melatonin values. In addition, peak values and peak to trough values will be calculated and compared between groups. Wake-to-bed slopes of cortisol will be calculated by subtracting the bedtime sample value from the sample collected immediately upon awakening and divided by the number of hours separating these two samples [31]. Dim light melatonin onset (DLMO) is estimated by comparing evening melatonin concentrations to the mean levels obtained from samples collected during daylight hours. Other potentially rhythmic variables (blood glucose, oral pH and oral temperature) will be visually reviewed for rhythmicity and if applicable analyzed by similar methods.

The correlation between clock gene expression and sleep parameters (e.g., sleep quality, MEQ-category, AHI, and other sleep parameters (S5 File)) will be investigated through Spearman’s rho in correlation matrices. Additional potentially confounding variables will be added to these matrices. This includes variables related to diet, body composition, medication, physical activity and media device usage.

Significant findings from the correlational matrices will be further evaluated by longitudinal analyses (e.g. linear regression). In these analyses, measures of circadian rhythmicity e.g., acrophase of clock gene expression, will be used as dependent variables. Independent variables will be ‘group allocation’, BMI, gender and age. Variables with an insignificant effect will be skipped from the model. Subsequently, other variables with a potentially confounding influence as identified in the correlational matrix will be added to the model. The most appropriate model will be selected based on the Akaike Information Criterion (AIC), with preference given to the model having the lowest AIC score [32].

In all tests, a p-value below 0.05 is considered significant.

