### Strength and limitations

The primary strength of our study lies in its minimally invasive, at-home sampling approach. This method allows participants to collect data on their own, with minimal interference to daily routines.

A notable limitation of our study is the relatively broad inclusion criteria for participants with mental health conditions. This inclusivity, while enriching the diversity of our sample, introduces variability in comorbidity, medication use and symptomatological characteristics among participants. Consequently, this heterogeneity may decrease our ability to detect significant effects and dilute the statistical power needed for potential subgroup analyses. All participants are outpatients primarily referred through psychiatric treatment units and user organizations by certified health professionals. Health professionals are aware of the study design and scope, and therefore, participants are expected to have stable symptoms and be deemed adequately cognitively fit to complete the entire study trial. While explicitly stating symptom stability and neurocognitive health as inclusion criteria would have added transparency to our trial, the recruitment process likely ensures that our study population resembles other studies with explicitly stated criteria. For example, Adan et al. (2024) excluded patients with induced disorders, those with unstable symptoms or not in remission, and those with conditions affecting the assessment process (i.e., neurological and neurocognitive disorders) [42]. Moreover, since symptom characteristics are not specifically measured, we cannot compare participants with predominant negative or positive symptomatology. Sampling schedules are tailored to each participant’s sleep-wake cycle, differing from the fixed schedules commonly used in hair follicle sampling studies [37,43,44]. This customization better aligns with participants’ usual rhythms, allowing those with varying sleep patterns to adhere to the schedule without altering their wake or bedtimes. This is especially important since participants in the OB+SCH and OB+BD groups are expected to have significantly later sleep onset and longer sleep periods [45,46]. Additionally, our schedule enables most employed participants (mainly in the CON and OB groups) to conveniently collect samples at wake-up, during lunch breaks, and after work hours.

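### Timing the cosinor from each participant's own sleep offset removes any phase delay shared with sleep and shows longer sleep as an earlier acrophase; no clock-time acrophase is stated alongside it

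*Protocol article*

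**What the plan says.** Under Statistical analyses, the article fits a 24-hour cosine to each person's 48-hour profile in non-linear mixed effects models, "thereby allowing for the estimation of amplitude, acrophase, and mesor for each group". It continues: "Derived variables will be compared between groups using the non-obese control group as the reference". The time origin is then fixed: "Cosine analyses will be individualized relative to participants objectively measured mean sleep offset time". The hormones follow: "The same procedure will be used for the secondary measures of rhythmicity i.e. salivary cortisol and melatonin values".

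Acrophase is used again later in the same section. In the regressions, "measures of circadian rhythmicity e.g., acrophase of clock gene expression, will be used as dependent variables", with group allocation, BMI, gender and age as the initial predictors. Before that, "The correlation between clock gene expression and sleep parameters" is examined with Spearman's rho.

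On sleep timing, Strength and limitations says that "participants in the OB+SCH and OB+BD groups are expected to have significantly later sleep onset and longer sleep periods". That section defends tailoring the sampling times (adherence and respect for usual rhythms). It gives no reason for re-timing the analysis. Nowhere does the article state an acrophase on local clock time, or say that acrophase is to be read as a phase angle to waking.

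**The concern.** Individualizing the cosine relative to sleep offset is read here in its natural sense: each person's time zero is their own mean wake time. The reported acrophase is then clock-time acrophase minus sleep offset.

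That is harmless for group comparison if the groups wake at similar times on average. The article expects otherwise. Later onset plus longer sleep means later offset, so a larger value is subtracted in OB+SCH and OB+BD than in the reference group. The acrophase contrast then mixes two things: where the molecular or hormonal rhythm lies in the day, and when the person wakes.

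At stake is what the acrophase comparison and the acrophase regressions can conclude. A null difference could hide a real delay that the clock and sleep share. An earlier acrophase could arise from longer sleep alone. There is also mathematical coupling: sleep offset is part of the outcome, which may then be related to sleep-timing variables.

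**Working it through.** **The plan's own figures.** The power calculation gives 17 per group for mesor and 16 for amplitude, and no figure for acrophase. It states no effect size or SD, so these numbers cannot be rebuilt independently. Back-solving a two-sided unpaired t-test at 80% power gives d = 0.991 for 17 and d = 1.024 for 16. Nothing below depends on them.

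**Inputs from the article.** Origin at each person's mean sleep offset; acrophase compared with the control group; 20 per group; hair samples at awakening, every six hours and at bedtime, for two days; later onset and longer sleep expected in the psychiatric groups. The article gives no hours for these sleep shifts, so 0 to 2 h is assumed for each.

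**Algebra.**
- Shift in sleep offset = S + L.
- Group difference in acrophase on clock time = P.
- Group difference on the sleep-offset scale = P − (S + L).

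Special cases:
- Delay fully shared with sleep offset, P = S + L: the difference is 0.
- Clock moves with sleep onset only, P = S: the difference is −L.
- Clock unchanged, P = 0: the difference is −(S + L).
- Delay larger than the sleep shift, P > S + L: the excess stays visible as a delay.

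For S and L each from 0 to 2 h and P between 0 and S + L, the difference runs from 0 (P = S + L) to 0 − (2 + 2) = −4 h. It is never positive in that range.

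**Check by simulation.** The simulation compared 20 with 20, sampling hair at wake, +6 h, +12 h and bedtime over two days. Individual least-squares cosinor fits stood in for the mixed model, with 400 replicates. Assumed: amplitude 1, noise SD 0.3, wake-time SD 1 h. Clock phase was set to follow 0.7 of each person's wake deviation plus independent variation of SD 0.7 h. The true phase SD is then √(0.7² + 0.7²) = 0.99 h on clock time and √(0.3² + 0.7²) = 0.76 h after re-timing.

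| P, S, L (h) | Clock-time difference (p < 0.05) | Sleep-offset difference (p < 0.05) |
|---|---|---|
| 0, 0, 0 | 0.00 h (6%) | +0.02 h (5%) |
| 1, 1, 0 | +0.98 h (71%) | +0.01 h (5%) |
| 2, 2, 0 | +2.01 h (100%) | 0.00 h (4%) |
| 0, 0, 1 | +0.01 h (4%) | −0.97 h (86%) |
| 1, 1, 1 | +0.98 h (70%) | −1.01 h (85%) |
| 1.5, 1, 1 | +1.50 h (95%) | −0.51 h (32%) |
| 2, 1, 1 | +2.01 h (100%) | 0.00 h (6%) |
| 2, 0, 0 | +1.98 h (100%) | +1.98 h (100%) |

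The differences match the algebra. Mesor and amplitude agreed on both scales in every row. The percentages depend on the assumed SDs and on how closely phase follows wake time; the differences in hours do not.

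**Coupling.** With A the clock-time acrophase and O the sleep offset, Cov(A − O, O) = Cov(A, O) − Var(O). If A and O were independent with equal SDs (an illustration only), the correlation of the re-timed acrophase with sleep offset would be −1/√2 = −0.71, with no biological link at all.

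**The case against.** Acrophase relative to waking is a legitimate quantity. The article's Background describes physiology in relation to the sleep-wake cycle and speaks of misalignment, and phase relative to waking speaks to exactly that. On that scale an earlier acrophase is a real change in phase angle, so calling it spurious would be wrong. Alignment may also help: in a group model without individual phases, unaligned curves would flatten the group amplitude. All of this stands, and it is why the sleep-offset version should be kept. Making clock time the main scale would be a preference, not a correction.

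Some stronger readings are tempting, and the article does not support them:

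- *The analysis is blind to phase delay.* Only the part shared with sleep offset cancels; the last row of the table shows a 2 h delay intact.
- *All rhythm measures are affected.* The sentence covers cosine analyses. DLMO and the wake-to-bed cortisol slope are not stated to be re-timed, and sleep timing itself is measured directly.
- *The protocol predicts a delayed clock.* It predicts later and longer sleep, and says nothing about the direction of clock-gene phase.
- *Work schedules fix wake times in the comparison groups.* The article says only that "our schedule enables most employed participants (mainly in the CON and OB groups) to conveniently collect samples at wake-up". That describes convenience, and the point does not need the inference.

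It can also be said that a condensed article may leave a clock-time acrophase to a fuller plan, and that it could be recovered by adding sleep offset back. That is true, but the article does fix a time origin, compares acrophase between groups on it, and names acrophase as a regression outcome without saying what the quantity means.

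**Conclusion.** The point holds for cosinor acrophase of clock genes, cortisol and melatonin, and for the regressions that use it. The group difference on the stated scale is P − (S + L), which follows from the time origin alone. Given the sleep pattern the article expects, S + L is expected to be above zero in OB+SCH and OB+BD. A shared delay then contributes nothing, and extra sleep moves the acrophase earlier.

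In size, P = S = L = 1 h gives −1 h where clock time gives +1 h. A shared 1 h delay was significant in 71% of simulated studies on clock time and in 5% after re-timing. The hours of shift, SDs and noise are assumptions, so these percentages are illustrations and not forecasts.

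The reach is limited to one of three cosinor parameters, and not one that was powered. Mesor and amplitude, fitted for each individual, do not depend on the origin. The coupling matters only where sleep-timing variables are related to the re-timed acrophase. The article does not list every sleep parameter in its main text, so that is a possibility and not a stated analysis.

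**What to change.** Also fit the cosinor on local clock time and compare clock-time acrophase between groups and in the acrophase regressions. The article describes date and time marking for the hair tubes. For saliva it describes individualized schedules, so recorded times should be used where they exist and scheduled times otherwise.

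Keep the sleep-offset version and label it phase angle to waking. State before analysis which of the two supports conclusions about delayed or advanced phase. Where the sleep-offset acrophase is related to a sleep-timing variable, note that the two share a component.

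The cost is one extra model fit on data already being collected, and one more phase parameter to report and count for multiplicity.
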